### Data collection

In the inclusion visit, the health professional will gather the relevant medical data and history (illnesses, medication, alcohol consumption and psychoactive substances) from the patient's clinical record, after checking and completing it together with the patient. Then, relevant data on behaviour and risk-perception of suffering from an RTI, and data on previous traffic accidents will be collected.

A yearly follow up via telephone is expected to be performed.

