### Study variables

#### We dispose of two data collection instruments in order to carry out this study

-A survey, which will be carried out by health professionals in a face to face interview. Data will be obtained from the clinical register, and double-checked by the researcher and patient during the visit.

In this survey, the following will be noted: 1. Demographic data: age, gender, civil status, place of origin, level of studies, social class (according to the categories proposed by the Spanish Epidemiology Society). 2. Medication: long-term medication, acute medication (taken in the last 30 days). 3. Chronic health conditions related to higher risk of RTI (Table 3). 4. Alcohol consumption (measured using the AUDIT-C test). 5. Consumption of psychoactive substances (cocaine, ecstasy and others) during the last year, as self-reported by the patient and self-declared dependency level of psychoactive substances in the last month. 6. Estimated level of perception risk, as assessed by the health professional, and rated using a scale from 0 (no risk) to 10 (maximum risk). 7. Driving data: type of driver's license, length of time driver's license held; type of vehicle most usually driven (moped, motorbike, car, others); professional driver (y/n); time spent driving in hours per week; type of road usually used (urban, motorway or others); safety behaviours (use of seatbelts, use of helmet, use of car seats for children and adherence to speed limits). 8. Collision background in the last year (with or without injury); History of medical attention for traffic road injuries in the last year. 9. Self-declared self medicating. 10. Self evaluation of state of health (using the SF-12 test). 11. Self-perception of risk. Individuals will be asked to score their own risk for RTIs, when compared to subjects with their same gender and age, rated in a scale from 0 to 10.

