### Statistical analysis

The characteristics of the population will be outlined using a descriptive univariant analysis, calculating the average, standard deviation, median, minimum and maximum values for continuous variables, and frequency and percentages for categorical variables.

The results of the descriptive part will be expressed with their confidence interval (CI 95%). In order to investigate the distribution of the risk factors associated with suffering an RTI according to age and gender, bivariant comparisons will be carried out using the Chi-square test between categorical variables and the Student's t-test between continuous and categorical variables. In order to analyse the association between the risk perception of an RTI (low/medium/high) and the different risk factors considered, an unconditional binary logistical regression model will be implemented. For the risk perception considered as an ordinal scale, a multiple lineal regression will be implemented. For the selection of the variables for the multivariate model, the methodology proposed by Hosmer-Memeshow [57], Cobo [58] and Greenland [59] will be implemented. In the initial multivariate model, the significant bivariate level variables will be introduced, based on the level of significance p = 0.25 and the variables considered to be clinically relevant. Confusion, interaction and co-linearity factors will be analysed. The adjustment of the model will be evaluated using the Hosmer-Lemeshow test and the area under the curve.

All statistical tests will be carried out with a confidence level of 95% and supposing a bilateral contrast. The analyses with be carried out using the statistics package SPSS.

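### The risk-perception analysis for secondary objective 3 names a binary logistic model for a three-level outcome, gives no dichotomy and no main model, and the self-score is asked after the exposures have been reviewed

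*Protocol article*

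**What the plan says.** Secondary objective 3 (Objectives) relates self-perceived risk of a road traffic injury to chronic conditions, medication and psychoactive substances.

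Statistical analysis gives two models. The first is for "the association between the risk perception of an RTI (low/medium/high) and the different risk factors considered, an unconditional binary logistical regression model". The second follows at once: "For the risk perception considered as an ordinal scale, a multiple lineal regression will be implemented". On model checking, the section says: "The adjustment of the model will be evaluated using the Hosmer-Lemeshow test and the area under the curve".

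The face-to-face survey (Study variables) holds two ratings on a 0-10 scale. Item 6 is made by the professional: "Estimated level of perception risk, as assessed by the health professional, and rated using a scale from 0 (no risk) to 10 (maximum risk". Item 11 is made by the patient: "Individuals will be asked to score their own risk for RTIs, when compared to subjects with their same gender and age".

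Data collection sets the order of the visit. Illnesses, medication, alcohol and substances are taken "from the patient's clinical record, after checking and completing it together with the patient". The next sentence reads: "Then, relevant data on behaviour and risk-perception of suffering from an RTI, and data on previous traffic accidents will be collected".

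**The concern.** There are two separate problems, one of analysis and one of measurement.

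**Analysis.** The outcome has three levels and the model takes two. Someone must later merge two levels or drop one, and the article gives no rule for doing so. It gives no cut-points for low, medium and high, and does not say whether the professional's or the patient's rating is meant. With a second model for the same objective and no order of precedence, the choice of cut and of model could be made after the results are seen.

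**Measurement.** The exposures in objective 3 are discussed with the patient shortly before the outcome is scored, in an interview run by the same professional. That discussion may change the score, and no later analysis can separate its effect from a real association.

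**Working it through.** **1. The plan's own sample size.** Inputs from Sample size calculation: two-sided alpha 0.05, proportion 0.5, precision 0.05.

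n = 1.96² × 0.5 × 0.5 / 0.05² = 384.15, rounded up to 385 per age group; 4 × 385 = 1540. The plan's figures reproduce. The total is used below only as the base for effective sample sizes.

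**2. Model against outcome.** Low/medium/high has three levels; binary logistic regression needs two. A standard binary logit routine given an outcome coded 0/1/2 refuses to fit. In their standard form, the Hosmer-Lemeshow test and the area under the curve also need a two-level outcome. So the named model and the named checks both presuppose a dichotomy that the article does not give.

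**3. What merging would cost.** Assumption, not in the documents: the underlying score is roughly normal. Efficiency is relative to the ungrouped score.

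- Median split: 2/π = 0.637; 0.637 × 1540 ≈ 980.
- One-third/two-thirds split, cut at z = 0.431, normal density 0.3636: 0.3636² / (1/3 × 2/3) = 0.1322 / 0.2222 = 0.595; 0.595 × 1540 ≈ 916.
- Three equal ordered groups: (0.3636² + 0 + 0.3636²) / (1/3) = 0.793; 0.793 × 1540 ≈ 1220.

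**4. Dependence on the cut.** This is an illustrative simulation with N = 1540. None of its other inputs come from the documents: exposure prevalence 30%, a latent shift of 0.15 SD, and groups 0-3, 4-6 and 7-10. There were 400 runs, 150 for the ordinal model. In the last run the groups held about 38%, 51% and 10% of subjects.

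| Analysis | Power |
|---|---|
| Linear regression, 0-10 score | 0.76 |
| Proportional odds, three levels | 0.71 |
| Binary, low vs medium + high | 0.55 |
| Binary, low + medium vs high | 0.38 |

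The two binary rows differ only in which pair of levels is merged.

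**5. Which rating is the outcome.** Objective 3 speaks of self-perception, which points to item 11. Statistical analysis says only risk perception, and item 6 is also labelled as a perception of risk. No passage states that low/medium/high is a grouping of either score.

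**6. Order of questions.** The order rests on the word that opens the second Data collection sentence, not on the item numbers, since the numbered list gives contents rather than a stated asking order. Self-perception is listed last there and last again in the telephone survey, after new diagnoses, medication and substances. Difficulties and limitations of the study does not mention question order.

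**The case against.** The strongest reply is that objective 3 is not left without a usable analysis. Linear regression on the ungrouped scale is planned in the next sentence. It is workable for an 11-point score and uses all the information. This stands. A reader might infer that the objective has only an unfit model, and the article does not support that. The losses in step 3 apply only to the grouped analysis.

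A second reply is that the Hosmer-Lemeshow test and the area under the curve suggest that a dichotomy was intended, and that cut-points may be in a fuller document. The absence of cut-points alone would not be a finding. What remains is that the article does name a model, and it conflicts with the outcome in the same sentence.

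On question order, a reader might infer that the outcome is contaminated and the association inflated. The documents show the order, not an effect. An upward shift is plausible, but the article's Chronic health conditions section says that risk generally falls when conditions are treated and controlled, so a review of the record could also reassure some patients. The article does plan a pilot of the survey, though it does not say that the pilot will look at order.

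Finally, this is one of three secondary objectives, the main aim is descriptive, and the article disclaims causal conclusions. That limits the severity.

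**Conclusion.** The point holds at moderate severity. The binary logistic analysis of low/medium/high cannot be run as written, the outcome rating is not identified, and neither of the two models leads. If two levels are formed, efficiency is about 59-64%, against about 79% for three ordered groups. These figures assume a roughly normal score and the cuts shown, and they do not describe the planned linear regression. That low/medium/high derives from the item 11 self-score is a likely reading, not a stated fact.

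The question order is a separate and weaker point. It leaves the self-score open to priming, and neither the size nor the direction of any effect can be taken from the documents. The main aim and its sample size are unaffected.

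**What to change.** **Analysis section.**

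- State that the outcome for objective 3 is the patient's 0-10 self-score (item 11).
- Replace the binary model with proportional-odds (ordinal) logistic regression, on the 0-10 score or on low/medium/high. Say which, and give the cut-points if groups are used.
- Name this as the main model for objective 3 and add a check of proportionality. The two-level fit checks no longer apply in their standard form.
- Keep the linear regression as a sensitivity analysis.

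**Questionnaire.** Ask item 11 before the record review, and so before the professional's own rating. Put the risk-perception item first in the yearly telephone survey too, so that baseline and follow-up use the same order. For any interviews already held in the present order, list the order as a limitation.

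**Cost.** A few sentences in the analysis section and a reordered form; no extra data or subjects.

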### Quality control

The variables collected during the interview with the health professional will be reviewed and checked against the patient's clinical record during the same visit. Coordination meetings will be held with the collaborating researchers periodically. Any confusing or missing data will be revised by one of the investigators who will ask for explanations from the relevant investigator. Data collection booklets will be read using Teleform technology. The introduction of the data into the database as well as quality control will be carried out by a trained person with ample experience using Teleform. The interviewers carrying out the telephone interview will be trained and accredited periodically in order to ensure the maximum quality of data collection.

### Difficulties and limitations of the study

In this study the relationship of risk factors of suffering an RTI will be evaluated; however, this does not apply to causality assessment, which would need a different specific study design.

There may be subjects who, although are assigned to one of the participating centres, do not have an open clinical register there because it is the first time they have visited the clinic or because the record is on paper. In these cases, the clinical data will be collected during the inclusion visit.

The computerised clinical registers (eCAP™ software or similar) may not be correctly updated in some cases, due to their recent addition to the clinic. The researchers will complete the information in the inclusion visit and through the telephone interview.

There are some difficulties related to the measuring instrument (telephone interview and face to face interview), for ethical and legal reasons (consent form) as well as validity (there are no valid surveys designed to this effect). The researcher will carry out a pilot study to rate the difficulties in completing the survey.

Only those health and medication problems more often found in our field will be analysed in this study.

Alcohol intake and the consumption of psychoactive substances will be considered self reported. Biological tests will not be carried out because the objective is to obtain the data under the same conditions of actual clinical practice carried out in primary care visits.

The generalisation of the results will be limited to an urban population.

### Ethical aspects

The study will be carried out according to the principles contained in the Helsinki Declaration and its successive reviews and the Good Clinical Practice standards. The LESIONAT study protocol obtained approval from the corresponding Ethics Committee (CEIC IDIAP Jordi Gol).

Consent form: the information will be provided verbally and in writing. The study subjects will have sufficient opportunity to ask about study details. Printing of the consent form will follow the rules contained in the Helsinki declaration as stipulated in article 12 under the first title of the Royal Decree 15/1999.

Data confidentiality: in this study, only researchers and monitors/auditors will have access to the information on the participating subjects.

## Discussion

There are various motives that justify the importance of this study. Primary health care is an advantageous location to carry out preventive interventions in RTI. In our country, according to data provided by the Primary Health Care Information System, 75% of the population consults a general practitioner at least in their life, and the average number of visits is between 5 and 6 yearly. Furthermore, public health cover in Spain is practically universal. This makes primary health care an ideal place for the study and implementation of preventive measures in the RTI field. These could include warnings from the side effects of certain medication, the effects of psychoactive substances on driving skills to the importance of the control and monitoring of chronic or acute illnesses that help the patient elaborate a real reception of their physical state and capacity to drive [60-62].

RTI pose health problems that are extremely high in magnitude and in social and health repercussions. The Catalan Public Health Plan contemplates this intervention as a priority objective, and so establishes the following main aims for 2010: 1. To reduce by 20% the mortality rate associated with RTI in the main 3 population groups where they are most frequent (see introduction). 2. To reduce by 50% the mortality rate associated with RTI in men and women from 15 to 24 years old. 3. To reduce by 50% the mortality rates associated with RTI in drivers linked to an excessive intake of alcohol. 4. To reduce by 25% the prevalence of severe injuries associated with RTI in the 3 main population groups (see introduction).

The elements evaluated in this study (medication, chronic health conditions, consumption of psychoactive substances), are often managed in the Primary Care field and are therefore registered in medical records. Moreover, these are aspects that are inherently related to the Primary Health Care field which means that the date is quite complete and difficult to attain in other existing registers.

The improvement in the basic knowledge of risk levels of suffering from an RTI that this study aims to achieve is a necessary first step for the definition of preventative activities in primary health care in the near future.

The research team sets out the possibility of creating a group with the population group, and establishing telephone monitoring within it to investigate the prospective appearance of RTI, and the factors associated with them. With this idea, the included subjects will be asked for their consent, and to provide a contact phone number and a preferred time of day for posterior contact.

Regarding the bibliographic impact of this study and after thoroughly reviewing the available bibliography, we did not find any studies similar to the project that we propose. Therefore, we believe that the originality of the questions that we raise (taken from a primary health care approach) provided added value.

## Note

* "LESIONAT": Niveles de Riesgo de sufrir una **LESION **por **A**ccidente de **T**rafico en atención primaria"
